## 3. The Extended Back in Action Battery Protocol

### 3.1. Balance Test

Patients perform a double-leg stability test and single-leg stability tests on the Zebris Balance Force Plate, starting with the non-injured leg. While maintaining stability for 10 s on one leg with arms crossed in front of the chest, the contralateral leg needs to be flexed and is not allowed to touch the ground. If balance is lost, the test has to be repeated [36]. The center of pressure is calculated and the sEMG records the muscle activity for a later calculation of time to peak, onset, offset and EMG force-relation.

### 3.2. Jumps

#### 3.2.1. General Criteria

One practice trial with submaximal power (80% of the maximal power) is given, followed by three subsequent test trialsHands are placed on the hips during the jumpsStarting position in the center of the plate, with feet parallel and shoulder-width apartKnee and hip joints are extended during the flight phaseSoft landing in the center of the 3D force plate with knee over toe position, stable leg axisSingle-leg landing: the contralateral leg is not allowed to touch the ground, otherwise the test is stopped immediately

All tests are explained in detail and demonstrated by the tester. The subject is given time to ask questions about the performance of the jumps. All tests are guided by the same examiner.

#### 3.2.2. Double-Leg Countermovement Jump (DL-CMJ)

The patient bents the knees until a semi-squat (knee ～90°), hips flexed, and then jumps explosively upward, trying to reach maximum height in the shortest possible time [37]. 

#### 3.2.3. Single-Leg Countermovement Jump (SL-CMJ)

The subject stands with one leg in the center of the plate and performs the jump as described above. The uninjured leg is tested first followed by the injured leg [37].

#### 3.2.4. Double-Leg Drop Jump (DL-DJ)

Starting from an upright position on the top of a vaulting box, the subject drops down from the box onto the center of the force plate considering the shortest possible ground contact time (<250 ms). This is followed by an immediately performed “vertical push-off action as quickly and as explosively as possible in order to perform the highest possible jump in the shortest possible time; thereby using an eccentric-concentric muscle action” [38]. The second landing is performed gently and with a stable leg axis on one leg in the center of the force plate.

#### 3.2.5. Single-Leg Landing (SL-Landing)

Starting from an upright position on the top of a vaulting box the patient takes a step forward and drops down onto the center of the 3D force plate. The landing is performed softly and with a stable leg axis on one leg. The patient must hold the position for five seconds without losing the balance before stepping off the force plate. The uninjured leg is tested first followed by the injured leg.

### 3.3. Jump Coordination

The jump coordination path is performed with the Speedy Basic Jump Set (TST Trendsport, Grosshöflein, Austria).

#### 3.3.1. Speedy Jump (SL-SJ)

The patient performs a coordination parkour as quick as possible without breaks. Then, 16 single-leg jumps through a course of red (forward-backward-forward jumps) and blue (sideways jumps) hurdles has to be completed. The hips have to be parallel during the performance. The contralateral leg is not allowed to touch the ground and the limbs are not allowed to touch the hurdle [36]. Time is taken with the stopwatch and the mean value is determined for each course. The sEMG records muscle activation, and 3D movement is tracked by the Azure Kinect DK.

#### 3.3.2. Quick-Feet-Test (SL-QFT)

The patient completes 15 steps in and out with one foot at a time, while being allowed to use the arms to keep the balance. A repetition is defined when the starting leg returns to the initial position. In case of a mistake or a step on the speedy pole, the test is stopped immediately [36]. Time is taken with a stopwatch and the tapping rate is counted. The sEMG records muscle activation, and 3D movement is tracked by the Azure Kinect DK.

### 3.4. Isometric Strength Tests

#### Gluteus Medius (G Med)

The patient lies supine with the pelvis fixed straight on an examination table, arms lay along the upper body, and the extremity to be tested is abducted by 30°. Starting with the uninvolved leg, the examiner fixes the expander two centimeters proximal to the lateral malleolus. No support from the hands or the opposite limb is allowed during the test. On command the patient pulls the leg to the side evenly and without momentum (4–6 s) while the tester fixes the expander with the help of a weight. It is important that only the muscle group to be tested, the abductor muscles of the hip, is activated. The sEMG records the muscle activation.

### 3.5. Questionnaire

The patients complete the International Knee Documentation Committee (IKDC), the ACL-Return to Sport Injury Scale (ACL-RSI) and the Tegner Activity Scale (TAS). The patient-reported results on symptoms, recovery and functionality of the knee are crucial and of great importance as they represent the patient’s subjective assessment in addition to the objective biomechanical analysis.

### 3.6. Biomechanical Measurements

#### 3.6.1. SEMG and MVC

Prior to electrode placement the skin is cleaned and degreased with alcohol. Surface electrodes with a two cm center-to-center distance are attached along the direction of the muscle fibers on the evaluated muscle bellies. The signals are registered with 16-bit accuracy at a sampling rate of 1500 Hz and stored for subsequent analysis using Noraxon DTS unit (Noraxon USA). The EMG signals are filtered with a Butterworth high-pass filter (cutoff frequency 10 Hz) and a low-pass filter (cutoff frequency 500 Hz). The sEMG signal from the evaluated muscles are measured continuously during the modified BIA test battery.

The collected data is normalized to a reference value. Maximum voluntary contraction (MVC) is performed separately for each muscle investigated before the test trials. The MVC contractions is performed against a static resistance. The parameters of each muscle are expressed as a percentage of its MVC (%MVC).

#### 3.6.2. 3D Force Plate

Kinematic data is recorded with the 3D force plate Bertec FP4060-08 (Bertec^®^, OH, USA). The piezoelectric force plate provides data on forces and moments in three dimensions (Fx, Fy, Fz, Mx, My, Mz). The Bertec assesses the forces and moments acting at the contact point where the force is applied.

#### 3.6.3. Motion Capture Camera Setup

We are using the Microsoft Azure Kinect DK, a 3D marker-less motion capture camera system, to track the participant’s maximum valgus and varus knee position during the landing maneuvers. For this study, three cameras capture motion data synchronously at 30 Hz. They are placed in a circle around the subjects with approximately 120° spacing (one frontal view and two back-side views), fixed on tripods 90 cm above the ground and placed approximately three meters from the circle center. The motion capture system is synchronized to the sEMG system and force plate using an illuminated ball controlled by the sEMG software. This ball is placed to be seen by one camera. From the color stream of this camera, we infer the ball’s on and off phases. Subsequently, the synchronization shift is calculated.

The Azure Kinect Body Tracking SDK delivers 3D joint positions and orientations for each joint segment. From this, 3D knee angles are obtained by regarding the left and right ankle, knee, and hip joint positions by calculating the angles between the hip-knee and knee-ankle vectors. Additionally, the local 3D joint segment orientations are used to calculate flexion and extension, abduction and adduction, and internal and external rotation. The resulting kinematic and angular data is filtered using a 4-th-order Butterworth filter with a cutoff frequency of 10 Hz.

Studies show good reliability when using the Azure Kinect for Motion analysis purposes [29]. So far, the Azure Kinect camera has been evaluated for gait analysis and slower functional movements [31]. Although the movement of subjects during the protocol is very fast, especially for the quick feet and countermovement jumps, we are only interested in the maximum varus and valgus knee angles during the landing phase. Therefore, a sampling frequency of 30 Hz is regarded as sufficient as we are not analyzing the entire complex functional movement. For this purpose, the camera would have to be evaluated against a marker-based motion capture system. Furthermore, compared to video camera systems, where only 2D information can be retrieved, the 3D system allows for the calculation of 3D angles and therefore provides more insightful data. Especially this marker-less motion capture offers huge advantages as the time-consuming marker placement can be alleviated and is thus easier to implement in everyday clinical practice.

## 4. Data Analysis and Planned Statistical Analysis

All data are presented in a descriptive manner, including anthropometric data and absolute measured values. Side-to-side differences are calculated for all SL tests, using the limb symmetry index (LSI). Therefore, absolute values of the ACL-reconstructed leg are divided by the values of the unaffected leg and multiplied by 100. For the stability, quick feet and speedy tests LSI is calculated by dividing the measured value of the unaffected leg by the value of the ACL-reconstructed leg and multiplied by 100 according to the calculation done in the study by Herbst et al. [17].

Power is quantified in the sagittal plane and defined through force and velocity. This parameter is directly extracted from the force plate data and reported as extracted. It is assessed for jumping during loading phase and total jump height. Power is based on peak power calculations for the lower extremity, which is defined in newton for maximal applied force during contraction. Additionally, it will be interpreted in the context of recent LSI-papers.

Descriptive quantitative data are calculated as the mean ± standard deviation. The Kolmogorov-Smirnov test is used to test the normality assumption. To compare the variances across the means of the three groups we use ANOVA repeated measures. Wilcoxon and Friedman-Test are used as well to calculate between-group differences.

All statistical analyses are performed using SPSS (IBM SPSS Statistics, New York, NY, USA). The significance level for all statistical tests is set a priori to 0.05. A post-hoc power analysis is conducted when significant effects are found.

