Soft or rigid orthotic devices may support feedback strategies through skin contact and thus increase the subjective feeling of safety, resulting in a willingness to perform. In addition, braces and orthoses provide patients with security (even if only psychologically) but are not mechanically proven. The immediate clinical relevance is that orthotic devices either positively or negatively influence the tested performance on RTS or not.

For sporting performance and benefits to be taken from orthotic devices, the feedforward and feedback strategies model is becoming increasingly important. Feedforward and feedback control are generally explained as mechanisms to restore homeostasis in an organism [23]. Therefore, feedback can be described as a response to a sensory detection (e.g., unstable joint position during landing maneuvers), and using previous experience (e.g., jumping exercises) to make an appropriate modification (e.g., adjustment of knee position). On the other hand, feedforward control describes the preparatory action that occurs before an event. Experiences are initially brought into pre-activation. When repeatedly performing a jump, the athlete can better estimate how much force must be used to optimize the performance. Restoration of functional stability in the knee joint occurs through unconscious dynamic control in preparation for and in response to the movement [23]. Therefore feedforward, as an anticipatory strategy, and feedback, as an action occurring in response to the sensory detection, are helpful strategies to achieve the movement goal and optimize training in rehabilitation [23]. Feedforward is mainly based on experience with an expected task. A good reproduction of real effects occurs when no specific preparation for a complex task is carried out, because the more complex the task, the less feedforward mechanisms can take effect [23,24].

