### 2.1. Study Design

This study is a randomized, prospective, single-blind clinical trial with a three-group cross-over design. Due to the design of the study, complete blinding is not possible. Statistical analysts are blinded on the groups to be compared. The randomization procedure and allocation are done through a person who was not further involved. [name] are responsible for the test setup and finally carry out the tests.

Patients are only informed about the performance but not about the target character of the tests. After receiving written informed consent, three patients are randomly assigned to either group A, B, or C (Table 1) and therefore run the test battery with rigid orthosis, soft brace and without aids in a cross-over order.

The bioelectrical activity of the gluteus medius and semitendinosus muscles are recorded using sEMG according to Surface ElectroMyoGraphy for the Non-Invasive Assessment of Muscles (SENIAM) guidelines [25]. Surface electrodes are placed on the involved and uninvolved limbs.

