### 2.3. Procedure

The examination is performed in a single session, including three runs of the modified BIA test battery.

The patients are asked to abstain from unaccustomed strenuous exercise for at least 24 h before the testing and avoid eating a heavy breakfast in the morning before the test and no rich meals within two hours of the test. They are advised to wear comfortable sports outfits and indoor sports shoes. Only the double-leg and single-leg stability tests are carried out barefoot.

SEMG electrodes are applied to all participants on the ACL-reconstructed and unaffected legs on gluteus medius and semitendinosus muscles to measure muscle activation throughout the whole test battery.

After block randomization to determine the group, participants complete the test battery as presented in Table 2. For fatigue reasons, the unaffected limb is only tested in the first run. The best performance from each trial is selected for analysis.

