## Figures and Tables

**Table 1 healthcare-11-00513-t001:** Individual group test setup.

Run	Group A	Group B	Group C
1	orthosis	brace	no aid
2	brace	no aid	orthosis
3	no aid	orthosis	brace

**Table 2 healthcare-11-00513-t002:** Description of the planned consecutive activities during the measurement session [17,35].

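### The device comparison names no run (period) term and no lead test, although device order is randomised over three runs in one session

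*Protocol article*

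**What the plan says.** Section 2.1 describes a "randomized, prospective, single-blind clinical trial with a three-group cross-over design". Table 1 gives three cyclic orders: orthosis-brace-no aid, brace-no aid-orthosis, and no aid-orthosis-brace. Each device therefore appears once in each run. Section 2.3 puts everything on one day: "The examination is performed in a single session, including three runs of the modified BIA test battery".

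The article gives two reasons why performance may change from run to run. Section 2.3 cuts testing because of tiredness: "For fatigue reasons, the unaffected limb is only tested in the first run". The Introduction describes gains from repetition: "When repeatedly performing a jump, the athlete can better estimate how much force must be used to optimize the performance".

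Section 4 then states the analysis: "To compare the variances across the means of the three groups we use ANOVA repeated measures. Wilcoxon and Friedman-Test are used as well". The rank tests are aimed at the same differences as the ANOVA. A Kolmogorov-Smirnov test of normality is listed just before, but no sentence says that its result decides which test counts. The significance level is 0.05 for every test.

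**The concern.** In a crossover with three periods, the period is part of the design and normally part of the model. If performance drifts over the three runs and the model holds only patient and device, the drift goes into the error term. The device test then loses power, and a real device effect may be missed. That matters here because the Objectives section expects to tell coaches, athletes and medical staff whether they need have concerns about devices, so a non-significant result on Hypothesis 1 could be read as reassurance.

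The second issue is separate. Two omnibus tests of one contrast, each at 0.05 and neither in the lead, leave open which p-value is reported.

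**Working it through.** **The plan's own figure.** Section 2.2 gives N = 27 for 90% power at alpha 0.05, a large effect and 3 degrees of freedom, in a fixed-effects ANOVA. With a noncentral F, lambda = f² × N, df1 = 3 and df2 = N minus the number of groups, N = 27 is reproduced at f = 0.8. At f = 0.4 the same formula gives 93. This is a between-patient calculation, so it does not fix a within-patient device effect. The checks below therefore use a device effect that gives about the planned power.

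**Inputs.** From the article: 28 patients, the three orders in Table 1, three runs, alpha 0.05. As 28 is not divisible by 3, the orders are taken as 10/9/9. Assumed, because the article gives no value: normal errors; one device shifted by 0.87 within-patient SD; and a linear run trend of d within-patient SD per run, with d from 0 to 1 in either direction.

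**Step 1: power with no trend.** lambda = 28 × 0.87² × 2/3 = 14.13 on 2 and 2 × 27 = 54 df, which gives power of about 0.92.

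**Step 2: error term without run.** With run effects (-d, 0, +d), the run sum of squares is n × 2d², pooled into 2(n - 1) df. The error variance is multiplied by 1 + 2nd²/[2(n - 1)]. For n = 28:
- d = 0.25: 1 + 3.5/54 = 1.06
- d = 0.5: 1 + 14/54 = 1.26
- d = 1.0: 1 + 56/54 = 2.04

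**Step 3: simulation** (20,000 trials per setting, Table 1 orders). Ranges cover which device is shifted and, at 0.5 and 1.0, the direction of the trend.

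| Trend per run (SD) | RM-ANOVA, no run term | Friedman | ANOVA with patient, run, device | Points lost by RM-ANOVA |
|---|---|---|---|---|
| 0 | 0.91-0.92 | 0.80 | 0.91-0.92 | 0 |
| 0.25 | 0.89-0.91 | 0.76-0.78 | 0.91-0.92 | 0-2 |
| 0.5 | 0.83-0.88 | 0.66-0.72 | 0.91-0.92 | 3-9 |
| 0.75 | 0.72-0.82 | 0.49-0.60 | 0.91-0.92 | 10-20 |
| 1.0 | 0.54-0.70 | 0.28-0.41 | 0.91-0.92 | 21-38 |

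With devices evenly spaced instead (-0.5, 0, +0.5 SD), the worst case at 1.0 SD per run is 0.514 against 0.914, a loss of 40 points.

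**Step 4: type I error per outcome, no device effect.**

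| Trend per run (SD) | RM-ANOVA, no run term | ANOVA with run | Either RM-ANOVA or Friedman significant |
|---|---|---|---|
| 0 | 0.051 | 0.052 | 0.076 |
| 0.25 | 0.044 | 0.051 | 0.067 |
| 0.5 | 0.024 | 0.051 | 0.042 |
| 1.0 | 0.003 | 0.049 | 0.006 |

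With skewed errors and no trend, the either-test figure is 0.077. If three uncorrected pairwise Wilcoxon tests may also be chosen from, it is 0.126.

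**Step 5: bias.** With 10/9/9, the mean run number is 55/28 for the orthosis, 56/28 for the brace and 57/28 for no aid. The largest device contrast shifts by 2d/28: 0.036 SD at d = 0.5 and 0.071 SD at d = 1.

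**The case against.** **A condensed article may leave model terms to a SAP.** Section 4 does not say that run is excluded, and a SAP could add it. That stands as a caution. But the article does commit to named tests, two families for one contrast, and adding run is a concrete improvement to that stated choice.

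**The rank tests may be a fallback.** The normality test comes just before them, so the intent may be ANOVA if normal and rank tests if not. That is possible, but the rule is not written, and the wording reads as parallel use.

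**A steady drift is not established.** Fatigue and practice pull in opposite directions, cutting the testing is itself mitigation, and the Introduction also says that anticipation helps less in complex tasks. This stands. The trend is an assumption, and near zero the loss is negligible.

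Four stronger readings are tempting but not supported:
- *Both harms occur together.* They largely do not. At 0.5 SD per run the either-test error is 0.042, and where choosing a p-value inflates error, little power is lost.
- *Unequal orders bias the comparison.* Step 5 shows that the shift is negligible.
- *Patients drop out of the analysis through failed tests.* For quick feet, "In case of a mistake or a step on the speedy pole, the test is stopped immediately", but the article does not say that the attempt cannot be repeated. Section 3.1 has a failed balance test repeated, and jumps have three test trials with the best analysed.
- *Section 4 compares sequences, because groups A, B and C are sequences.* This is terminology. Every patient uses all three devices, and a repeated-measures test compares those.

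**Conclusion.** The point holds in a limited form. As written, the device analysis names no run term and no lead test, in a design built on randomised run order.

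The power loss depends on a run effect that the article does not quantify: negligible up to about 0.25 within-patient SD per run, moderate at 0.5 and serious near 1.0. The error is on the conservative side, so the risk is a missed device effect. These sizes rest on a linear trend, normal errors and a device shift of 0.87 within-patient SD.

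The p-value choice matters in the opposite situation, when the run effect is small: about 0.07-0.08 per outcome in place of 0.05, if the significant one of ANOVA and Friedman is reported. If the normality test is meant to select the analysis, writing that rule down would answer this part but would not supply the run term.

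**What to change.** Name one primary analysis of the device comparison with patient, run and device terms: a linear mixed model (SPSS MIXED) with fixed device and run and random patient, or the equivalent ANOVA. Report the pairwise device differences with 95% confidence intervals. Keep Friedman and Wilcoxon as labelled sensitivity analyses.

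The cost is a change of wording and two error degrees of freedom: 84 observations - 28 patients - 2 for device = 54, and 52 once run is added. No new data are needed, because the assigned order already fixes the run of each device. With no trend, the run-adjusted model has the same power, 0.91-0.92.

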## 5. Discussion and Expected Results

The purpose of the present study was to investigate the impact of orthotic devices and to analyze muscle activation and strength on functional stability of the knee during the modified test battery six months after ACLR.

It might be possible that soft braces or rigid orthoses improve functional performance during the modified BIA test battery. However, it is also possible that patients may be hindered in performing the test by wearing these aids, resulting in a decrease in functional performance.

As already mentioned, feedback and feedforward strategies play a major role in the completion of this test battery as well as in the general practice of sports [23,24].

We assumed that an ACL injury as well as ACLR negatively influence the mentioned feedback and feedforward strategies. Therefore, athletes may benefit from consistent and long-term use of soft braces or rigid orthoses at this time until they reach their initial performance level.

On the other hand, if the performance deteriorates due to the wearing of soft braces or rigid orthoses, the fundamental use of these aids in the rehabilitation process would have to be discussed and investigated more closely.

In addition to functional performance, the psychological aspect of wearing soft braces or rigid orthoses should also be considered.

Through to semitendinosus stripping with only partially regeneration of the tendon and postoperative immobility it might be possible that the sEMG results of the medial knee flexor show a strong imbalance of muscle activation patterns between the affected and unaffected limb and thus show worse results in the BIA test battery. In this case one could discuss the following aspect. Since the ischiocrural muscles act as agonist of the ACL function and as a medial stabilizer one could focus more on targeted neuromuscular training in order to strengthen these muscles. On the other hand, one could also discuss whether the use of other ACL grafts such as peroneus longus split could be an alternative to the semitendinosus graft as it has no primary influence on the biomechanics of the knee.

Ueno et al. found that increased knee adduction is associated with pelvic tilt and reduced gluteus medius strength and could therefore increase the risk of ACL injury [39]. Moreover, in a scoping review, Rinaldi et al. emphasized the impact of gluteal muscle strength on knee position during walking, running, jumping and landing [28]. However, Llurda-Almuzara et al. pointed out that gluteus medius and semitendinosus, among other muscles, showed no association between DKV and neuromuscular response [40]. Due to the controversial statements, this study aims to investigate on the influence of gluteus muscle strength and semitendinosus muscle activation and their possible influence on DKV and pelvic drop.

In summary, the obtained results will provide further information on the rehabilitation process. Accordingly, conclusions can be drawn, and training adapted to avoid reinjuries, e.g., due to muscular imbalances. However, if the tests provide excellent results, this would be a reason to establish jump tests earlier in the rehabilitation process in order to be able to release people earlier into their regular everyday life. For personal and economic reasons, this could be especially important for professional athletes so that they can hopefully return to their preinjury level as quickly as possible.

